Workplace productivity impairment will be assessed in patients using the Work Productivity and Activity Impairment Questionnaire: General Health V2.0 (WPAI:GH) and in caregivers using the Work Productivity and Activity Impairment Questionnaire: General Health Care Giving V2.0 (WPAI:GH-CG) [25]. These are six-item questionnaires assessing the effects of the patient’s health problems (WPAI:GH), or the effects of caregiving for the patient’s health problems (WPAI:GH-CG), on the individual’s ability to work and perform daily activities. A schedule for these assessments is shown in Table 2.

**Table 2 Tab2:** Schedule of assessments

	Enrolment	1 month^a^	3 months^a^	6 months^a^	12 months^a^	18 months^a^	24 months^a^
Informed consent provided by patient and caregiver (note that caregiver consent is optional for patient study inclusion)	X						
Retrospective chart review (collection of demographic and medical history data)	X						
Ongoing clinical data, including clinical outcomes, laboratory measures, medication dose/schedule, resource utilisation, medication adherence^b^		X	X	X	X	X	X
GETE^c^		X		X			
CLDQ^b^	X				X		X
EQ-5D-5L (patient)^d^	X		X	X	X	X	X
EQ-5D-5L Proxy (caregiver)^d,e^	X		X	X	X	X	X
WPAI (patient)^c^	X		X	X	X	X	X
WPAI (caregiver)^c^	X		X	X	X	X	X

*CLDQ* Chronic Liver Disease Questionnaire, *EQ-5D-5 L* Euroqol-5 Dimension-5 level measure, *GETE* Global Evaluation of Treatment Effectiveness questionnaire, *WPAI* Work Productivity and Activity Impairment questionnaire

^a^Target dates only; flexible depending on patient response

^b^To be collected at all clinic visits but not at fixed time intervals; clinic visits will be scheduled by investigator and patient according to normal management and not defined by study protocol

^c^To be collected at the clinic visit closest to the indicated study date; no additional clinic visits to be scheduled for study participation

^d^To be requested for patient completion via paper submission or online portal or at clinic visit closest to the indicated date; clinic visit may not be required

^e^Australia, UK, Ireland, France and Germany, where the proxy response has been validated

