Although encouraging, these cost-effectiveness analyses were modelled using RCT data and their results therefore need to be confirmed with real-world evidence. PROSPER will address this need by providing valuable real-world information on the impact of rifaximin-α 550 mg treatment in Europe and Australia on both the direct costs (e.g., hospitalisation rate, duration of hospitalisation) and indirect costs (e.g., work productivity) of HE. PROSPER could also afford a better understanding of the burden and natural history of HE, and of variability in disease management between different countries and regions. Additionally, PROSPER is likely to provide the type of evidence required by payors and decision bodies to confirm whether rifaximin-α 550 mg treatment represents a good use of economic resources (as indicated by cost-effectiveness models), thereby ultimately allowing access to the right treatment for the right patients.

Since the findings and implications of real-world studies are often limited by bias, PROSPER has been specifically developed to minimise bias, in terms of both its design and the robust statistical methodology it employs. As such, it is broadly in line with the International Society for Pharmacoeconomics and Outcomes Research (ISPOR) Good Research Practices Taskforce guidelines, which state that the choice of study design may strengthen the ability to address potential biases and confounding in prospective observational studies, separately from the analytic and statistical approaches employed [20]. The details provided in the present article also address the guidelines’ recommendation that the reasoning behind all study design and analytic choices should be transparent and explained in the study protocol [20].

The ISPOR guidelines acknowledge the increasing importance of real-world studies in informing health policy decisions and highlight the consequent necessity for rigour and transparency when conducting such studies [20]. In addressing these concerns, it is anticipated that the findings of PROSPER will be widely applicable to clinical practice and may help inform future approaches to HE management.

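### Work productivity (WPAI) can be collected only at routine clinic visits, although EQ-5D-5L, due on the same dates, may be returned by paper or portal

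*Protocol article*

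**What the plan says.** Table 2 of the Protocol article (Study assessments) schedules patient WPAI, caregiver WPAI, EQ-5D-5L and its caregiver proxy at enrolment and at 3, 6, 12, 18 and 24 months. The collection route is set by footnote.

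- The WPAI rows, "WPAI (patient)^c" and "WPAI (caregiver)^c", carry footnote c: "To be collected at the clinic visit closest to the indicated study date; no additional clinic visits to be scheduled for study participation".
- The EQ-5D-5L rows carry footnote d: "To be requested for patient completion via paper submission or online portal or at clinic visit closest to the indicated date". It adds that a "clinic visit may not be required".
- Footnote b states that "clinic visits will be scheduled by investigator and patient according to normal management and not defined by study protocol".
- Footnote a describes the time points as "Target dates only; flexible depending on patient response".
- Footnote e limits the proxy EQ-5D to Australia, the UK, Ireland, France and Germany. Methods/design names Denmark as the principal recruiting country.

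The Abstract lists workplace productivity of patients and caregivers among the secondary endpoints. The Discussion promises evidence on "indirect costs (e.g., work productivity) of HE".

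**The concern.** Two questionnaires of the same length, due on the same dates, are given different routes, and the article gives no reason. One can reach the study without a visit; the other cannot. Since routine care decides when visits happen, whether a WPAI form exists depends on how often the patient is seen. That frequency may vary with illness and possibly between the cohorts, so missing WPAI data are unlikely to be a random subset.

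The caregiver form carries the same footnote, so it is lost whenever the patient's visits lapse, even if the caregiver would willingly respond. If EQ-5D-5L supplies the quality-of-life input to the planned QALYs, then QALYs and productivity losses could come from different subsets of the same study. Adjustment in the analysis can deal with some selective missingness but cannot recover forms that were never requested.

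**Working it through.** **The plan's own figures.** The article gives no visit frequency and no expected WPAI completeness. Its only sample-size figure concerns hospitalisation: 100 events / 0.45 = 222.2; 222.2 / 0.90 = 246.9, rounded up to 247 per cohort; 2 × 247 = 494. This reproduces the stated 247 and 494. WPAI does not enter it.

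**The two routes side by side (Table 2, Study assessments).**

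| | WPAI, patient and caregiver | EQ-5D-5L and proxy |
|---|---|---|
| Length | six items | six items |
| Due (months) | 0, 3, 6, 12, 18, 24 | 0, 3, 6, 12, 18, 24 |
| Route | nearest routine clinic visit | paper, portal or nearest clinic visit |
| Obtainable without a visit | no route stated | yes |

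**How capture depends on attendance (assumed visit patterns).** Take the five post-enrolment targets (3, 6, 12, 18, 24 months) and routine visits every *k* months from enrolment up to month 24. Assign each target to the nearest post-enrolment visit and count the different visits used. That count is the number of separate WPAI measurements.

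- *k* = 1, 2 or 3: 5 of 5.
- *k* = 4: 4 or 5. Months 4 and 8 are equally near to the 6-month target; if month 4 is used, it serves both 3 and 6 months.
- *k* = 6: 4. Month 6 serves both 3 and 6 months.
- *k* = 8: 3.
- *k* = 9 or 12: 2.

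Under footnote d, EQ-5D-5L can be requested at all five targets in every one of these cases.

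**Leaving clinic care (assumed 3-monthly visits that then end).**

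- Last visit at month 3: 1 WPAI form, against 5 possible EQ-5D requests.
- Last visit at month 6: 2 forms. Nothing new for 12, 18 and 24 months, so 3 of 5 targets are lost.
- Last visit at month 9: 3 forms (3, 6 and 9 months, the last standing in for 12). Nothing new for 18 and 24.
- Last visit at month 12: 3 forms. Nothing new for 18 and 24.

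The same counts bound the caregiver's WPAI, which has the same footnote.

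**Caregivers outside the proxy countries.** Denmark is not among the five countries in footnote e. There the caregiver receives no proxy EQ-5D, so no caregiver mailing exists to which WPAI could simply be added.

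**The case against.** The strongest reply is that different routes for different questionnaires are neither a contradiction nor a misstatement. The study is observational and deliberately adds no visits, WPAI is secondary, and where patients are seen at least every 3 months nothing need be lost. All of that stands, and it limits the weight of the point. It does not explain why the remote route is withheld from WPAI. Study design rules out changes to the management of HE; a posted or online form changes no management and is already accepted for EQ-5D-5L. Footnote c might also be read as a timing rule only, with some remote route in the full protocol. But footnote d lists its routes explicitly and footnote c names only the visit.

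CLDQ is visit-bound too (footnote b). That is true, but it has 29 items and a different schedule, and it is not the productivity measure.

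Four stronger readings are tempting, and the document does not support them.

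- *WPAI ends when treatment ends.* Study design collects up to 24 months of data from study entry for patients on or off rifaximin-α, and Statistical analysis expects discontinuation during follow-up and undertakes to consider it. A patient off treatment who still attends still completes WPAI.
- *The cohort comparison is biased by a known amount or in a known direction.* No attendance data are given by cohort or by treatment status.
- *The absence of visit windows, or of a rule allotting one form to one time point, is a fault.* A condensed article may leave both to the full protocol or SAP. The counts above show only how many separate measurements can arise.
- *GETE needs the same change.* It carries footnote c, but it is due at 1 and 6 months, with no EQ-5D request at 1 month to join, and it does not measure productivity.

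**Conclusion.** The point holds as a design improvement. As printed, WPAI capture for patient and caregiver depends on the patient's clinic attendance, and it ends when visits end, while EQ-5D-5L due on the same dates does not. The size cannot be derived from the document. Under the assumed visit patterns it runs from no loss (visits every 1 to 3 months) to three of the five post-enrolment measurements lost (visits every 9 or 12 months, or visits ending at month 6), and to four of five if visits end at month 3. That attendance varies with illness, and possibly by cohort, is plausible but not shown. The consequence is confined to a secondary endpoint and the indirect-cost evidence built on it. The primary hospitalisation endpoint and the figures of 247 per cohort and 494 overall do not change.

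**What to change.** In Table 2, move patient WPAI and caregiver WPAI from footnote c to footnote d. Request both with the existing EQ-5D paper or portal prompt at 3, 6, 12, 18 and 24 months, whether or not the patient is attending clinic; completion at a visit remains an option. In countries without the proxy EQ-5D, Denmark included, send the caregiver WPAI by the same paper or portal route to caregivers who have consented. Leave GETE as scheduled.

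The cost is a little more burden for participants and some questionnaire set-up, including a caregiver route outside the five proxy countries. The paper and portal channel already exists for patients, and no visits are added.

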### Sample size calculation

In observational studies where multivariable modelling is expected to be performed, the study should have at least 10 events for every variable included in the model. Therefore, in order to consider approximately 10 variables, 100 events would need to be observed in each of the study cohorts (patients receiving and not receiving rifaximin-α 550 mg). On the basis of an open-label maintenance study of rifaximin-α 550 mg in patients with HE [19], approximately 45% of patients would be expected to have experienced a hospitalisation within the first 12 months of follow-up. Assuming a dropout rate of 10%, approximately 247 patients would be required for each of the two cohorts, or 494 patients overall. Thus, a total study population of 550 would be sufficient to assess the primary endpoint of the study at an interim follow-up of 12 months, with additional precision following the full 24-month follow-up period.

### Statistical analysis

A primary aim of PROSPER will be to minimise any bias typically associated with observational studies. This will be achieved by the three-step comparative structure incorporated into the study’s design (as described above) and the associated statistical methodology. An overview of the statistical considerations is presented here.

The primary outcome of HE- and liver-associated hospitalisation rate will be analysed as a count, using either Poisson or negative binomial regression, depending on the level of observed dispersion. An offset term will be included to account for length of time eligible to experience a hospitalisation, accounting for mortality or other competing risk events. The primary outcome of duration of HE- and liver-associated hospitalisation (number of bed-days) will be analysed either as a continuous variable or a count, depending on the observed distribution. Methodologies such as median regression may be employed to account for the likelihood of right skew resulting from a small proportion of extended hospital stays. Comparison of the primary outcomes between treatment cohorts will adjust for key covariates using either multivariable regression analysis or a propensity score analysis (to be confirmed based on an exploratory review of the data). Due to the observational nature of the study, it is expected that some patients could change, discontinue or be non-compliant with therapy during the course of follow-up. These scenarios will be considered during statistical analysis and techniques that account for exposure to therapy will be applied, if applicable.

The rate of all-cause hospitalisation and the resulting duration of hospitalisation will be analysed in the same way as the primary endpoints. Numeric measures (e.g., CLDQ, EQ-5D-5L and GETE scores) will be analysed using a linear regression model, with longitudinal methodology to account for repeated measures, if applicable. Event-based variables and count data (e.g., AEs, HE episodes, mortality) will be analysed using Poisson or negative binomial regression, with offset terms to account for exposure time, length of time eligible to receive hospitalisation and competing risks (e.g., death); analyses will also adjust for underlying differences between cohorts (i.e., confounding factors). Time-to-event methods (e.g., Kaplan Meier analysis) will be used for variables such as time until death. Categorical demographic and clinical characteristics will be presented descriptively as frequency/percentage distribution and compared using a chi-squared test. Continuous demographic and clinical characteristics will be presented descriptively as means with 95% confidence intervals and compared using a Student’s *t*-test.

It is anticipated that additional analyses will include treatment adherence and switching, and the integration of survival data with QoL data, to assess quality-adjusted life-years (QALYs). Other exploratory analyses may also be conducted.

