**Conclusions:**

PROSPER will provide valuable real-world information on the effectiveness of rifaximin-α 550 mg in reducing the recurrence of HE, and its impact on the QoL and work productivity of patients and their caregivers. By providing data on both the direct costs (e.g., hospitalisation rate, duration of hospitalisation) and indirect costs (such as work productivity) of HE, PROSPER should help confirm whether rifaximin-α 550 mg treatment represents a good use of economic resources.

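### Median regression, the one technique named specifically for bed-days, is ill-suited to an outcome that the plan's own 45% figure makes zero for more than half of patients at 12 months

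*Protocol article*

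**What the plan says.** The protocol article (Study assessments) makes the number of bed-days resulting from HE- and liver-related hospitalisation part of the primary endpoint. Under Statistical analysis, this outcome "will be analysed either as a continuous variable or a count, depending on the observed distribution". The next sentence begins: "Methodologies such as median regression may be employed to account for the likelihood of right skew", and it ascribes that skew to a minority of patients with long stays. No other technique is named specifically for bed-days. All-cause bed-days, a secondary endpoint, are to be analysed in the same way.

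The Sample size calculation states that "approximately 45% of patients would be expected to have experienced a hospitalisation within the first 12 months of follow-up". The source is given as follows: "On the basis of an open-label maintenance study of rifaximin-α 550 mg in patients with HE". The cause of hospitalisation is not specified. The same section regards 550 patients as enough to assess the primary endpoint at a 12-month interim, with more precision at 24 months. Current status confirms that an interim analysis is planned.

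On the use of the results, the abstract says that "PROSPER should help confirm whether rifaximin-α 550 mg treatment represents a good use of economic resources", and it lists duration of hospitalisation among the direct costs.

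**The concern.** Bed-days per patient have two awkward features: a long right tail and a block of patients with none. The article addresses only the tail. A median resists a long tail, but once more than half of the values are zero the median is zero, however many days the admitted patients spend in hospital. At the 12-month interim, which the plan calls sufficient for the primary endpoint, the named technique could therefore return no contrast even if mean bed-days differ between cohorts.

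Three further points bear on the choice.
- The plan gives the hospitalisation-rate model an offset for time at risk, with mortality in view. A median of raw totals has no direct multiplicative equivalent.
- Restricting the analysis to admitted patients would remove the zeros, but it conditions on a post-baseline event that treatment may itself change.
- The economic purpose calls for mean bed-days per patient. A median does not scale up to total use.

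**Working it through.** **Inputs from the protocol article:** 100 events per cohort, 45% hospitalised by 12 months, 10% dropout (Sample size calculation); analyses at 12 and 24 months.

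**1. Reproduce the plan's figure.** 100 / 0.45 = 222.2; 222.2 / (1 − 0.10) = 246.9, rounded up to 247 per cohort; 2 × 247 = 494. This matches: "Assuming a dropout rate of 10%, approximately 247 patients would be required for each of the two cohorts, or 494 patients overall". It matches only with 45% used in both cohorts.

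**2. Zeros at 12 months.** 1 − 0.45 = 0.55. As 0.55 > 0.50, the median of bed-days over all patients is zero in each cohort. The share of zeros is higher if the 45% is all-cause, because the endpoint counts only HE- and liver-related stays.

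**3. Sampling variation.** The binomial probability that more than half of a cohort is hospitalised, at a risk of 0.45, is 0.059 with 222 patients and 0.048 with 275. Either cohort's sample median therefore exceeds zero only about 5–6% of the time.

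**4. If the 45% holds only for the rifaximin cohort.** The control median rises above zero once control risk passes 50%. That needs a risk ratio below 0.45/0.50 = 0.90, or a hazard ratio below ln(0.55)/ln(0.50) = 0.86.

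**5. At 24 months (assuming constant rates).**
- Constant hazard, same for all patients: 1 − 0.55² = 0.6975, about 70%.
- Gamma frailty with variance 1, where P(any) = m/(1 + m): m at 12 months is 0.45/0.55 = 0.818; at 24 months m = 1.636 and P = 1.636/2.636 = 62%.
- If the 45% is all-cause and 60% of admissions are HE- or liver-related (assumption), the frailty model gives m = 0.982 and P = 49.5%, still just below one half.

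**6. Illustration by simulation.** Assumptions: 222 patients per cohort, frailty as in step 5, mean stay 11 days, true 40% cut in admissions.

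| Setting | Studies with equal medians |
|---|---|
| 12 months, 45% in the control cohort | 92–94% |
| 12 months, 45% in the rifaximin cohort (control risk 0.818/0.6 = 1.364; 1.364/2.364 = 58%) | 1–2% |
| 24 months, 45% at 12 months in the control cohort | under 1% |

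The ranges are across separate runs. The ratio of mean bed-days averaged 0.61 in the first setting, close to the true 0.60. The rows should be read together: under the same true effect, the median contrast is almost always nil or almost always present, depending on where each cohort lies relative to 50%.

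**7. Equal risk, different length of stay.** With 45% in both cohorts and typical stays of 8 versus 16 days (lognormal, assumed), medians were equal in 85% of runs.

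**The case against.** The strongest reply is that the plan does not commit to median regression. Its governing rule is to choose a continuous or count analysis on the observed distribution. A mass at zero is part of that distribution, so the rule already permits a negative binomial model. The article calls its statistical section an overview, and the final model choice may lie in an analysis plan that is not shown. This stands, and it limits the severity. What remains is that the one example given for a primary outcome is justified by long stays alone and fits poorly with the plan's own planning figure.

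A reader might infer that the bed-days analysis cannot show a difference whatever the truth. The documents do not support that, for four reasons.
- The 45% comes from rifaximin-treated patients. Its use in both cohorts served to count events per variable and does not predict equal risk. A modest benefit lifts the control median above zero.
- Follow-up runs to 24 months, when risk probably exceeds one half.
- The plan requires covariate adjustment, and conditional medians can be above zero in high-risk strata.
- The endpoint wording could be read as length of stay among those admitted, where zeros do not arise, at the price of conditioning on a post-baseline event.

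It is also fair to say that an economic aim does not oblige every primary analysis to be on the mean scale, and that the plan does not exclude means.

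**Conclusion.** The point holds in a limited form and is a should-fix improvement. If 45% are hospitalised by 12 months in both cohorts, as the sample size assumes, about 55% of patients have zero bed-days. An unadjusted all-patient median at the interim is then expected to be zero in both cohorts and uninformative. This rests on three conditions: equal risk, zeros included, and no covariate adjustment.

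Outside those conditions the medians can differ. The size of the difference is then governed largely by which cohort crosses 50%, and it still does not estimate mean resource use. The 24-month risk of 62–70% assumes constant rates. The simulated percentages also depend on the assumed frailty and stay lengths; the 55% does not.

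**What to change.** Do not use median regression as the primary analysis of bed-days. Instead:
- analyse total HE- and liver-related bed-days per patient, zeros included, with a negative binomial or log-link generalised linear model, a log follow-up-time offset, and robust or bootstrap intervals;
- report adjusted mean bed-days per patient-year in each cohort, with their ratio and difference;
- use a two-part model (any stay; days given any stay) as sensitivity analysis, noting that its second part conditions on admission;
- apply the same approach to all-cause bed-days, which follow the primary method.

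This changes only analysis wording and needs no new data. The downside is that a mean is more sensitive to a few very long stays. The robust or bootstrap interval reflects that uncertainty, and the two-part model helps show where a difference arises.

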### Study design

PROSPER will be conducted under ‘real-world’ clinical practice conditions. Consequently, no changes to the management of HE patients will be made for the purposes of the study.

Once eligible patients have been recruited and consented to participate in the study, two data collection phases will be undertaken (Fig. 1). The first will be a retrospective phase, involving the review of the patients’ medical records and electronic hospital admissions data. Up to 12 months of data prior to study entry will be reviewed and collected. The level and nature of missing data will be assessed and accounted for in the statistical analysis plan, if necessary. The retrospective phase will be followed by a prospective phase, during which data will be collected from all patients either receiving rifaximin-α 550 mg (rifaximin-α 550 mg cohort) or not receiving rifaximin-α 550 mg (control cohort) from the point of study entry. Up to 24 months of data following study entry will be collected and analysed.

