### Study assessments

The study’s primary endpoint will be the HE- and liver-related hospitalisation rate and the resulting duration of hospitalisation (number of bed-days). Secondary endpoints will include the rate of all-cause hospitalisation and the resulting duration of hospitalisation (number of bed-days), mortality rate, and the number, duration and severity of HE episodes. Effects of treatment on the underlying liver disease will also be assessed as secondary endpoints using the Child-Turcotte-Pugh score, Model for End-stage Liver Disease (MELD) score or MELD-Na score (a modified MELD score including serum sodium [22]). In addition, the effectiveness of treatment will be assessed by the patient, caregiver and physician, using the Global Evaluation of Treatment Effectiveness (GETE) questionnaire. This consists of the single question ‘*How effective has [your treatment/the treatment] been in controlling [your/the patient’s] HE?*’, which is answered by choosing one of five responses: ‘*Complete control of HE*’, ‘*Marked improvement in HE*’, ‘*Limited improvement in HE*’, ‘*No appreciable change in HE*’ or ‘*Worsening of HE*’.

The safety of treatment with rifaximin-α 550 mg will be evaluated by assessing the frequency and nature of adverse events (AEs) and serious AEs. This will include classification of the severity of AEs and their relationship/causality in relation to medical treatment of HE.

The effects of treatment on health-related QoL will be assessed using the patient-reported Chronic Liver Disease Questionnaire (CLDQ) [23], the patient-reported Euroqol-5 Dimension-5 level (EQ-5D-5L) measure and the caregiver-reported proxy EQ-5D-5L:1 measure [24]. The CLDQ is a 29-item questionnaire assessing a wide range of physical, emotional and psychosocial QoL-related factors during the previous 2 weeks [23]. The EQ-5D-5L and proxy EQ-5D-5L are six-item questionnaires assessing the patient’s mobility, ability to self-care, ability to undertake usual activities, pain/discomfort, anxiety/depression and overall health status on the particular day in question [24].

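### The between-cohort comparison of non-serious adverse event rates may partly reflect how often each cohort is seen, and neither the offsets nor the confounder adjustment corrects for that

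*Protocol article*

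**What the plan says.** All references are to the protocol article.

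- **Safety measure (Study assessments).** "The safety of treatment with rifaximin-α 550 mg will be evaluated by assessing the frequency and nature of adverse events (AEs) and serious AEs". Severity and causality are also classified.
- **Model (Statistical analysis).** "Event-based variables and count data (e.g., AEs, HE episodes, mortality) will be analysed using Poisson or negative binomial regression". The same sentence provides offsets for exposure time, time at risk of admission and competing risks such as death. It then adds that "analyses will also adjust for underlying differences between cohorts (i.e., confounding factors". That adjustment makes this a comparison between cohorts.
- **Data collection after entry (Table 2).** The row reads "Ongoing clinical data, including clinical outcomes, laboratory measures, medication dose/schedule, resource utilisation, medication adherence". It carries footnote b: "To be collected at all clinic visits but not at fixed time intervals", and "clinic visits will be scheduled by investigator and patient according to normal management and not defined by study protocol".
- **Care (Study design).** The study is observational: "no changes to the management of HE patients will be made for the purposes of the study".

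The Table 2 row does not name AEs. The article states no other route by which non-serious AEs are captured after entry, and the AE model contains no term for visit or contact frequency.

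**The concern.** A person-time offset corrects for how long a patient was at risk. It does not correct for the chance that an event in that time was noticed and written down. For deaths and hospital admissions that chance should depend little on clinic attendance. For a mild or transient AE it can depend on attendance heavily, yet the plan puts AEs in one class with mortality under the same model.

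Attendance is decided by investigator and patient under normal management, with treatment known to both. A patient starting a new drug may be called back more often. A patient who stays well may be seen less. The direction is not known, so the bias cannot be assumed to be conservative.

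Confounder adjustment deals with differences that exist at entry. It can absorb differences in attendance that follow from baseline severity. It does not absorb differences that arise after entry because of the treatment itself.

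At stake is the between-cohort statement on non-serious harms, which could show an excess that does not exist or hide one that does. The primary endpoint is not affected by this point.

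**Working it through.** **The plan's own figures.** The article gives no AE rate and no visit rate, so there is no stated figure to reproduce on this point. The one related calculation, the sample size, does reproduce: 100/0.45 = 222.2, and 222.2/0.90 = 246.9, rounded up to 247 per cohort or 494 overall. It concerns hospitalisation and says nothing about AE detection. Its only use here is the 223 evaluable patients per cohort in step 3.

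Everything below rests on assumed visit patterns. The true AE rate is the same in both cohorts throughout, so any ratio other than 1.00 is spurious.

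**Step 1: regular visits with a recall window.** Suppose visits occur every *I* months and an AE is recorded if the next visit falls within *w* months of onset. The share recorded is min(1, *w*/*I*). The spurious rate ratio is the share at the shorter interval divided by the share at the longer.

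| Visit intervals (months) | *w* of 3 or less | *w* = 4 | *w* = 6 |
|---|---|---|---|
| 3 v 3.5 | 3.5/3 = 1.17 | 1.00 | 1.00 |
| 3 v 4 | 4/3 = 1.33 | 1.00 | 1.00 |
| 3 v 6 | 6/3 = 2.00 | 1/(4/6) = 1.50 | 1.00 |

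For 3 v 4 months with *w* between 3 and 4, the ratio is 4/*w* and falls from 1.33 to 1.00. The result therefore depends strongly on the recall window. It is independent of *w* only while *w* is no longer than either interval.

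**Step 2: two other detection models.**

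- *Irregular visits.* With visits at random times at rate *r* per year and a window of *w* months, the share recorded is 1 − exp(−*r·w*/12). For 6 v 4 visits a year:
  - *w* = 1: 0.39/0.28, ratio 1.39 before rounding the shares
  - *w* = 3: 0.78/0.63, ratio 1.23
  - *w* = 6: 0.95/0.86, ratio 1.10
  - *w* = 12: ratio 1.02
- *Mixed capture.* Let *s* be the share of the reference cohort's recorded AEs that are found only at visits, and *v* the ratio of visit frequencies. The ratio is (1 − *s*) + *s·v*. With *s* = 0.5 and *v* = 1.5 it is 0.5 + 0.75 = 1.25. With *v* = 1.25 it runs from 1.06 (*s* = 0.25) to 1.25 (*s* = 1). With *v* = 1 it is 1.00 for every *s*.

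**Step 3: would a spurious 1.25 be declared significant?** Assume 223 patients per cohort, 1 AE per patient-year, 1 year of follow-up and a two-sided 5% test. ln 1.25 = 0.223.

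- Poisson: SE = √((1 + 0.8)/223) = 0.0898, z = 2.48, significant in about 70% of studies.
- Negative binomial with dispersion 1: SE = √((2 + 1.8)/223) = 0.1305, z = 1.71, significant in about 40% of studies.

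**The case against.** The strongest reply has four parts.

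1. *The plan does more than offset for time.* This is correct. A reader might infer from the regression wording that time is the only thing accounted for, but the same sentence also covers competing risks and confounders. Adjustment may remove visit differences driven by baseline severity. What remains is any difference that treatment creates after entry.

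2. *Capture at clinic visits is an inference.* This is also correct. The Table 2 row refers to clinical outcomes without naming AEs, and the full protocol may describe how AEs are sought. But the article commits to a specific AE model, and safeguards elsewhere would have to go beyond that model to answer the point.

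3. *No difference in visit frequency is shown.* This stands. Both cohorts enter within 12 weeks of resolution of an overt HE episode associated with a hospital visit, are judged clinically eligible for the drug, and attend secondary or tertiary centres. The Discussion's UK before-and-after study reports fewer hospitalisations per patient after initiation (2.7 v 1.7), which shows that contact with care can change around treatment. Those are not clinic visits by cohort and give no size for the bias.

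4. *The safety evaluation is wider than a rate ratio.* This stands too. Nature, severity and causality are assessed, and serious AEs are named separately. The whole safety conclusion does not rest on this one comparison.

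**Conclusion.** The concern holds in a conditional form and for non-serious AEs. If visit frequency differs by cohort after entry because of treatment, the stated offsets and confounder adjustment leave the unequal chance of detection uncorrected, and the non-serious AE rate ratio may partly reflect attendance. This is a weakness of an analysis the article commits to, not a missing detail.

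The size cannot be fixed from the article. With no true difference and visits every 3 v 4 months, the spurious ratio is 1.33 for recall of 3 months or less and 1.00 for recall of 4 months or more. With equal visit frequency, or with AEs captured regardless of visits, the bias is nil.

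A reader might go further and conclude that the AE comparison is biased, or that all harm outcomes are affected. The documents support neither. They give no visit rates by cohort, and deaths and AEs leading to admission should depend far less on clinic attendance. The matter deserves correction because the article makes minimising bias a primary aim, but it concerns a secondary safety result.

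**What to change.** In the Statistical analysis section:

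1. Base the between-cohort harm conclusion on deaths and on serious AEs leading to admission, using the prospective admissions data already needed for the primary endpoint. All-cause hospitalisation is a secondary endpoint, so these data are not confined to HE and liver causes. The article names electronic admissions records only for the retrospective phase, so it should state that the prospective source is the same for both cohorts.
2. Report clinic visits per patient-year by cohort beside the AE results.
3. Label the between-cohort ratio for non-serious AEs exploratory, and add a sensitivity analysis that accounts for visit frequency. It should not be the sole analysis, because AEs may themselves prompt visits.

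Counting AEs only at the visit nearest each Table 2 target month would not equalise capture. There are six targets (1, 3, 6, 12, 18 and 24 months). Visits every 3 months supply five distinct nearest visits (3, 6, 12, 18 and 24), and visits every 6 months supply four (6, 12, 18 and 24).

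The cost is slightly more analysis work and a less prominent non-serious AE comparison. Serious AEs that did not lead to admission or death would fall outside the main harm comparison and should still be reported. No extra visits or patients are needed.
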